## Methods/design

### Study design

This study is a prospective, randomized, multicentre, controlled design, and it will be conducted from December 2021 to December 2024. We will recruit 176 participants from 5 hospitals in 3 different provinces (Yunnan province, Zhejiang province, and Shandong Province). The eligible participants will be randomly allocated to 2 groups in a 1:1 ratio. The randomization sequence will be computer generated by the Clinical Research Center of the Yunnan University of Chinese Medicine. Every participant will receive a 1-week treatment period and a 2-week follow-up. Basic information and outcomes will be assessed at baseline and after each week. The flowchart is shown in Fig. 1, and the schedule is shown in Table 1.

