### Sample size

A previous relevant study showed the effective rate of pediatric *Tuina* was 92.5% and Medilac-Vita was 72.5% [35]. Based on our own clinical experience, we consulted pediatric *Tuina* and physician experts. We anticipate an effective rate of 90% in the pediatric *Tuina* group and 70% in the Medilac-Vita group. Considering *α* = 0.05, 1-*β* = 0.90, *p*_1_ = 0.90, *p*_2_ = 0.70, *u*_0.05/2_ = 1.96, *u*_0.1_ = 1.282 [36], $$n=1641.4\times {\left[\frac{\left(1.96+1.282\right)}{\sin \sqrt[-1]{0.90}-\sin \sqrt[-1]{0.70}}\right]}^2$$ = 79.02 ≈ 79. With a drop-out of 10%, 88 FC children will be finally recruited in each group. Totally, 176 participants will be finally recruited in this study.

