### Statistical analysis

The statistician will perform statistical analysis by using SPSS 19.0 statistics software (IBM Co., Armonk, NY, USA) and GraphPad 7.04 statistics software (GraphPad Software Co., San Diego, California, USA). Continuous variables are presented as the mean and standard deviation (SD). While the nonnormally distributed variables are presented as the median and interquartile range (IQR). Categorical variables are described as numbers and percentages (%).

Before the comparison, the normality and homogeneity of variance will be tested. Normality of continuous variables (SBMs, CSBMs, m-BSFS, distress sensation, and glycerine enema rate) will be determined by *Shapiro-Wilk* test, *Kolmogorov-Smirnov* test, *Skewness*, and *Kurtosis*. Homogeneity of variance of continuous variables will be determined by *F* test, *Brown-Forsythe*, and *Bartlett’s* test. Independent-Sample *t*-test or nonparametric test (*Mann-Whitney* test) will be used when compared between two groups. Paired *t*-test or nonparametric test (*Wilcoxon* test) will be performed to compare within a group. For the categorical variables (effective rate), the *χ*^2^ test will be performed to evaluate the significance of the difference. The statistical analysis will be a 2-sided test with a significance level of 0.05.

The missing data were will be dealt with expectation maximization, last observation carried forward method or listwise deletion. Subgroup analysis will be conducted according to the subject’s age (< 4 years and ≥ 4 years), which depends on the normality and homogeneity of variance of the data.

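### EM or LOCF fill-ins would be tested as if observed: with about 10% filled in, EM by arm gives roughly 6-8% t-test error, while pooled EM or baseline-carried LOCF shrinks the effect by up to about 10%

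*Protocol article*

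**What the plan says.** All on this point stands in the protocol article.

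- Statistical analysis, on missing data: "The missing data were will be dealt with expectation maximization, last observation carried forward method or listwise deletion". No rule links a method to an outcome, a week or a reason for missingness.
- Same section, on tests: between groups, an independent-sample t-test or a "nonparametric test (*Mann-Whitney* test) will be used when compared between two groups"; within groups, a paired t-test or a "nonparametric test (*Wilcoxon* test) will be performed to compare within a group"; a chi-square test for the effective rate. No mixed model, multiple imputation or variance correction is named.
- Same section, on error level: "The statistical analysis will be a 2-sided test with a significance level of 0.05".
- Sample size: "With a drop-out of 10%, 88 FC children will be finally recruited in each group".
- Primary outcomes and Data collection: weekly SBMs and/or CSBMs are primary, with outcomes collected at baseline and at the end of weeks 1, 2 and 3.

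**The concern.** Each named test for a continuous outcome needs one value per child for each comparison (a pair of values for the within-group tests). None of them can use the uncertainty that comes with EM estimates. EM can therefore enter only as a single expected value per gap, and LOCF only as a single copied value. The text does not say outright that fill-ins are analysed as observed, but the listed tests leave no other route.

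Two things can then go wrong even if values are lost purely by chance. An EM fill-in has no residual scatter and still counts as a full observation, so the standard error can be too small. A fill-in that ignores the arm, or that copies a pre-treatment value, carries no treatment effect, so the difference can be pulled towards zero. At stake are the 0.05 level and the effect estimates for the primary outcomes.

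**Working it through.** **Inputs from the protocol.** Two-sided alpha 0.05; 88 per arm; 10% drop-out; 1:1 allocation; baseline plus three weekly assessments.

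**Assumptions not in the protocol.** 10% of values filled in, with 5% and 20% as a range; missingness completely at random and equal in both arms; normal outcomes with SD 1; correlation rho between outcome and predictor of 0 to 0.7; true effect 0.25 to 0.50 SD.

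**1. The plan's own figure.** With angles in degrees, arcsin√0.90 = 71.565 and arcsin√0.70 = 56.789. Then n = 1641.4 × [3.242 / 14.776]² = 79.02, so 79. 79 / 0.90 = 87.8, so 88 per arm and 176 in total. This reproduces. The protocol gives no error or bias figure for missing data.

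**2. EM by arm, closed form.** Let n = 88, n_obs = 88 × 0.90 = 79.2 and R² = rho².

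- True variance of an arm mean (unit SD): R²/n + (1 − R²)/n_obs.
- Variance the t-test would use: [R² + (1 − R²)(n_obs − 1)/(n − 1)] / n.
- Actual error: 2 × [1 − Φ(1.96 × √(used/true))].

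At rho = 0: true = 1/79.2 = 0.012626; used = (78.2/87)/88 = 0.010214; root of the ratio = 0.899; 1.96 × 0.899 = 1.763; error = 7.8%.

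| Filled in | rho 0 | rho 0.3 | rho 0.5 | rho 0.7 |
|---|---|---|---|---|
| 5% | 6.3% | 6.2% | 5.9% | 5.6% |
| 10% | 7.8% | 7.5% | 7.0% | 6.3% |
| 20% | 11.7% | 11.0% | 9.8% | 8.1% |

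**3. Simulation at 10% missing.** 88 per arm, no true effect, baseline as predictor, 3,000 runs per setting; Monte Carlo error is about 0.4-0.5 points. Cells give the actual error of a nominal 5% test.

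| Method and test | rho 0 | rho 0.3 | rho 0.5 | rho 0.7 |
|---|---|---|---|---|
| EM by arm, t | 7.6% | 7.7% | 6.9% | 5.8% |
| EM by arm, Mann-Whitney | 10.5% | 8.6% | 7.1% | 6.3% |
| EM by arm, paired t | 6.8% | 6.8% | 7.2% | 7.3% |
| EM pooled, t | 5.0% | 5.1% | 4.9% | 4.6% |
| EM pooled, paired t | 6.2% | 6.0% | 6.2% | 6.0% |
| LOCF, baseline to week 1, t | 5.1% | 4.9% | 4.8% | 4.5% |
| Listwise deletion, t | 5.0% | 5.2% | 5.0% | 5.0% |

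With week 1 also observed and week 3 missing, EM by arm gave 8.4%, 6.1% and 6.5% at rho 0.3, 0.5 and 0.7. Listwise deletion in the same runs gave 5.6%, 4.5% and 5.7%, so part of the 8.4% is simulation noise. LOCF gave 5.2%, 4.4% and 5.6%, in step with listwise deletion.

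**4. Size of the effect, true difference 0.50 SD, 10% missing.**

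- Pooled EM from baseline: filled children add no expected difference, so 0.90 × 0.50 + 0.10 × 0 = 0.45. Simulated: 0.448 (rho 0) and 0.445 (rho 0.5).
- LOCF, baseline to week 1: the same arithmetic, 0.45. Simulated: 0.450 and 0.445.
- Pooled EM at week 3 with week 1 observed, constant effect, rho 0.5: 0.469, a loss of about 6%.
- LOCF at week 3 copying week 1: expected 0.90 × d3 + 0.10 × d1, where d1 and d3 are the true differences at weeks 1 and 3. Constant 0.50 gives 0.50 (simulated 0.499). Waning from 0.50 to 0.25 gives 0.275 in place of 0.25 (simulated 0.277). Growing from 0.25 to 0.50 gives 0.475 in place of 0.50 (simulated 0.468).
- Listwise deletion: 0.498 and 0.496, with power about 87% against 90-91% with no data missing.

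**The case against.** The strongest reply has four parts.

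*A sound option is already listed.* Under completely random missingness, listwise deletion keeps 5% error and an unbiased effect. This stands, and it means the faults appear only if EM or LOCF is used. It does not clear the plan, because the wording leaves all three open and the other two can distort the result.

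*The 10% is a drop-out rate, not a stated share of filled-in values.* This also stands. The Drop out criteria count largely incomplete diaries as drop-out, and the Interventions section does the same for children who take other interventions. Fill-in may be meant only for smaller gaps. At 5% filled in, the closed-form t-test error is at most 6.3%.

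*Better prediction reduces the error.* Correct. With three other weeks observed and equal correlations, R² = 3rho²/(1 + 2rho). That is 0.375 at rho 0.5 and 0.61 at rho 0.7, giving about 6.7% and 6.0% at 10% filled in. At 5% filled in the latter is about 5.5%.

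*EM grouping and predictors belong in an analysis plan that is not shown.* Fair for those details, and they are not criticised as missing. The naming of single fill-in methods beside tests that cannot carry their uncertainty is a stated choice.

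A reader might infer that EM and LOCF alike must either push the error to 7-8% or shrink the effect by exactly the missing share. The documents do not support this. LOCF did not raise the error rate in any run, and at later weeks its bias can go either way. Pooled EM with an informative earlier week shrinks less than the missing share. A reader might also infer that a blinded analyst must pool the arms. That does not follow, because the two-group tests already need a group code, and the code can be masked.

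**Conclusion.** The concern holds in a conditional form. If EM is used by arm with about 10% of values filled in, a nominal 5% t-test has about 6-8% actual error and Mann-Whitney about 6-10%. If EM is pooled, or LOCF carries baseline to week 1, the between-group error stays near 5% but the difference shrinks by up to about 10%. LOCF at weeks 2-3 leaves the effect unchanged, shrinks it or inflates it, according to how the true effect changes over time. Listwise deletion has neither fault but loses some power.

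These sizes rest on completely random and equal missingness, normal outcomes, and the assumed filled-in share and correlations. EM by arm or pooled, and whether drop-outs are filled in at all, are not stated. The distortion is moderate, but it touches the primary outcomes and is cheap to remove, so the text should be changed.

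**What to change.** In the Statistical analysis section, delete single EM fill-in and LOCF for SBMs, CSBMs and the other continuous weekly outcomes. Name one method that carries the uncertainty of missing values:

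- a likelihood-based repeated-measures model on all observed weeks, with arm, week, arm by week and the baseline value, which needs no fill-in; or
- multiple imputation with arm, baseline and the other weeks in the imputation model, at least 20 imputations, combined by Rubin's rules.

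State also whether children who drop out are included in that analysis.

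The cost is wording and a little more programming. The four planned assessments suffice, so no extra children or data are needed. The downside is slightly wider intervals than single fill-in would show.

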## Discussion

Pediatric *Tuina* is a Chinese massage therapy based on the special meridian-acupoint theory of TCM. Due to the characteristics of pediatric *Tuina*, all manipulations are performed on the body surface. Under some circumstances, cloaks and other covering may be used to blind parents or guardians [37]. However, most parents hope that child’s symptoms get a quick relief, despite FC is not life-threatening. In case of the efficacy (sham *Tuina*) cannot be guaranteed, it easily leads to doctor-patient disputes. Therefore, this study set probiotics with definite efficacy as the control.

Sample size calculation should be based on the results of relevant high-quality studies by principle. Limited by the methodological flaws of the existing studies, there were no objective indicators (e.g., SBM, CSBM, BSFS, m-BSFS) as outcomes. The effective rate was most widely used in pediatric *Tuina* for FC. Therefore, the sample size of this study set an effective rate as a reference. However, this study also set the defecation frequency, stool form, and distress sensation those directly related to constipation as the outcomes. Under the circumstance that lumpy stool and difficult defecation, glycerine enema is usually used to assist defecate. Anal injection of glycerine enema can lubricate the colon to promote the excretion of stool. Therefore, glycerine enema rate can indicate whether difficult defecation and whether the child can complete defecating on his own. Other evaluation indicators such as Cleveland Constipation Score (CCS), Patient Assessment of Constipation Symptom (PAC-SYM), and Patient Assessment of Constipation Quality of Life Questionnaire (PAC-QoL) are not suitable for children with FC, because children (especially toddlers) could not express their feelings directly and accurately [38–41].

As a complementary and alternative therapy, standardization and quantification of massage manipulations have always been stumbling blocks which limit the scientific research and development of massage. The complex manipulations of massage determine that the robot can not completely replace the therapists. In China, pediatric *Tuina* is a medical treatment rather than a nursing skill. Although all manipulations will be performed by physicians with a master’s degree in pediatric *Tuina*, differences in manipulations may still exist between different physicians. In order to solve the differences, we will conduct unified training of pediatric *Tuina* before the study started. Electronic test glove which can measure pressure, amplitude, frequency, and angular velocity will be used to examine the therapist’s manipulation (Fig. 2 and Additional file 3).

**Fig. 2 Fig2:**
[figure not shown]
Electronic test glove

In conclusion, this study may be the first high-quality RCT to certify the efficacy, safety, and advantage of pediatric *Tuina*. Since the probiotics’ curative effect is questioned in recent years [23], this study also investigates the differences in defecation frequency and stool form between pediatric *Tuina* and probiotics for children with FC. Once the objectives are achieved, it could provide strong evidence support for the enactment of clinical guidelines for FC. Pediatric *Tuina* may become an officially recognized treatment by the state, it may also be included in the category of medical insurance. The international influence and recognition of TCM pediatric *Tuina* will be greatly enhanced. It can also enhance the professionals’ confidence in the treatment of FC by pediatric *Tuina* After the study is completed, academic conferences and training courses may be performed to disseminate the pediatric *Tuina* for FC in children.

### Trial status

This trial was registered on 16 May 2021. The trial is currently in the stage of unified training of pediatric *Tuina.*

## Data Availability

No data were used to support this protocol. The outcomes data of the trial will be published within the final study manuscript and as the attachment for access. The outcomes data will also be uploaded to the Chinese Clinical Trial Registry.

## Abbreviations

CPMA: Chinese Preventive Medicine Association
CRF: Case report form
CSBMs: Complete spontaneous bowel movements
FC: Functional constipation
FGID: Functional gastrointestinal disorder
IQR: Interquartile range
m-BSFS: Modified Bristol stool form scale
RCTs: Randomized controlled trials
SBMs: Spontaneous bowel movements
SD: Standard deviation
SPIRIT: Standard Protocol Items Recommendations for Interventional Trials
TCM: Traditional Chinese medicine
